### Randomization

Randomization will occur using computerized randomization with random numbers. To ensure adequate allocation concealment, the random allocation sequence was 1.) generated before patient enrollment begin, and 2.) by a member in the research group (LA) that is not involved personally with the patients. That is, is not part of the clinical setting were the study is implemented.

### Eligibility criteria

To be eligible to participate, patients must: 1) agree to participate in the study and sign written informed consent; 2) be aged between 18 and 65 years; 3) speak the language of the participating country (German, Polish or Danish); 4) have completed detoxification (if needed); 5) have been enrolled within 2 weeks of standard treatment; 6) not have any sensory or motor deficits complicating the provision of AATP (e.g. color-blindness, fine or gross motor deficits in upper extremities); 7) not fulfil diagnostic criteria for other substance use disorders; and 8) not have a severe psychiatric or neurological illness (e.g. psychotic disorders, mental retardation, dementia) or terminal somatic illness.

### Experimental and control groups

A total of 204 (68 patients from each country) fulfilling the eligibility criteria will be randomized into one of three groups: (A) AATP + TAU (*n* = 68); (B) VR-based AATP + TAU (*n* = 68), and (C) TAU (*n* = 68). The mean optimal effect of AATP among AUD patients is typically achieved after the sixths training session [32]. Therefore, group A and group B will receive six sessions (three sessions per week for 2 weeks; duration = 30 mins) of AATP and VR-based AATP, respectively, in addition to TAU. Group C will only receive TAU. The two experimental groups will begin treatment approximately 3 weeks before discharge from the inpatient clinics to measure the add-on effect and to ensure that the add-on treatment does not extend the treatment period.

#### Conventional approach- avoidance training program

Since the AATP builds on the experimental neuropsychological paradigm, the training is intertwined with the alcohol-AAT and consists of a pre-test, training, and post-test session.

In the AAT, patients are instructed to respond to either the *content* or the *format* of the presented pictures using a joystick. When responding to the content in the “stimuli-relevant” trials, they have to pull the joystick to approach pictures of alcoholic or non-alcoholic drinks and push the joystick to avoid the pictures. When responding to the format in the “stimuli-irrelevant” version, they must pull or push the joystick based on the color of the frame around the pictures of the alcoholic or non-alcoholic drinks. The color of the frame is interchangeably reversed (through randomization): a yellow frame requires a push response and a blue frame requires a pull response. Pulling the joystick increases the size of the pictures and pushing it decreases the size, generating a perception of approach and avoidance, respectively.

The pre-test for the AAT starts with practice trials in which patients learn to push and pull the joystick. Actual pre-test trials follow, with patients completing either the stimuli-irrelevant AAT or the stimuli-relevant version first in random order. In both versions, the pictures of alcoholic and non-alcoholic drinks are presented equally often in push and pull format. Following this, patients are requested to complete the avoid-alcohol training in the stimuli-relevant AATP. That is, during the training the patients are *only* instructed to respond to the *content* of the stimuli. In the training trials, 100% of the alcohol pictures come in push-format and 0% in pull-format, with reversed contingencies for pictures of non-alcoholic drinks. Half of the pictures used in the pre-test will also be applied in the training, and the half will be different to allow a test for generalization to untrained pictures. The post-test for the stimuli-irrelevant/stimuli-relevant AAT is almost identical to the pre-test: it presents both trained and untrained pictures of alcoholic (50%) and non-alcoholic (50%) drinks [19] (see Supplementary material for further description of the parameters [33]).

Before and after each session, patients will be requested to report their immediate level of cravings on a VAS scale (see Secondary outcome: cravings, self-efficacy, impulsivity and depressive severity and Cue-induced cravings sections for further details).

#### Approach- avoidance training program in virtual reality

In the VR-based AAT and AATP, patients are situated in a bar environment where drinks appear on a table in front of them. Similar to conventional AAT and AATP (delivered on a computer), the VR-based AATP consists of a pre-test, training, and post-test session, but patients are requested to respond to either the content or format of the presented beverages by pulling or pushing a VR controller instead of a joystick.

The pre-test for the VR-based AAT starts with practice trials in which patients learn to use the VR controller. This is followed by actual pre-test trials: patients complete the stimuli-irrelevant AAT first followed by the stimuli-relevant AAT. In the stimuli-irrelevant AAT, there is a colored outline around the beverages which patients must respond to. The colored outline is interchangeable reversed (via randomization), with a yellow outline requiring a push response and a blue outline requiring a pull response. In the stimuli-relevant AAT, patients must respond to the content of the bottles. Both versions present alcoholic and non-alcoholic drinks equally often in push and pull format. Patients are then requested to complete the avoid-alcohol training and respond to the *content* in the stimuli-relevant VR-based AATP. In the training trials, 100% of the alcoholic beverages come in push-format and 0% in pull-format. The contingencies are reversed for non-alcoholic drinks. Half of the beverages used in the pre-test will also be applied in the training, and the other half will be different to allow a test for generalization to untrained alcoholic. Similar to the conventional ATT, the post-test for the stimuli-irrelevant/stimuli-relevant VR-based ATT is almost identical to the pre-test.

In the VR-based AATP, pulling the VR controller will approximate the drink (will bring the drink closer) and pushing it will distance the drink, which we anticipate generates a more real perception of approach and avoidance, respectively, relative to the zooming feature in the conventional AATP. Further, the VR-based AATP will prompt patients to exercise more realistic movements compared to the conventional AATP, and the virtual bar context may make the setting appear more like real life. Also, a bar tender will be placing the alcoholic beverages onto the bar counter, which may enhance the amount of effort used to avoid and push drinks away. Patients will be seated on a bar stool in VR, and the alcoholic and non-alcoholic beverages will be depicted as high-poly objects to make the experience as realistic as possible (see Supplementary material for further description of the parameters [33]).

Similar to the conventional AATP, patients will be asked to rate state craving on a VAS scale before and after training.

#### Treatment as usual

The control group will not receive any add-on sham-training since prior studies testing the AATP did not find any difference between AATP-sham-training and no-training [19]. Patients in this group will be randomly assigned to complete the stimuli-relevant and stimuli-irrelevant AAT on either the PC- or VR-based bias assessment and will only be assessed at baseline and post-treatment (see Measures section). The conventional and VR-based AATP will be delivered by a trained research assistant.

### Measures

Socio-demographic factors, AUD diagnoses and severity, prior AUD treatment, psychiatric comorbidity, medication, behavioral inhibition and treatment goal will be assessed in the baseline interview (T1). Clinical outcome measures relating to alcohol consumption and cravings will be assessed at baseline, post-treatment, and 3-month follow-up (T1, T2, and T3). Additionally, experimental outcomes, including approach biases, cue-induced cravings and a response inhibition task, will be assessed at baseline and post-treatment (T1 and T2) (See Fig. 1 for an overview of the assessment and intervention timeline across countries). Finally, the patients will be assessed for concomitant treatment between the post-treatment and 3-month follow-up at the 3-month follow-up assessment (T3). The assessments will, like the interventions, be carried out by trained research assistants.

**Fig. 1 Fig1:**
[figure not shown]
Overview of the study design across assessment sites (countries). Abbreviations: AATP: approach-avoidance training programme; PC: personal computer; T1: baseline assessment; T2: post-treatment assessment; T3: 3month follow-up; VR: virtual reality. * Both add-on experimental AATP interventions starts 3 weeks before discharge

#### Baseline assessment instruments

The Mini-International Neuro-psychiatric Interview (MINI) for DSM-5 is a structured interview probing the 17 most common psychiatric diagnoses using dichotomous questions that ask for a yes/no response. The MINI will be used to establish the severity of AUD diagnoses as well as to screen patients for eligibility and detect psychiatric comorbidity diagnoses [34, 35].

The European version of the Addiction Severity Index (EUROP-ASI) is a semi-structured interview assessing sociodemographic variables as well as AUD severity and seven potential problem areas (alcohol use, drugs use, medical problems, psychiatric problems, family problems, employment/economy problems, and legal problems) [36, 37]. The EUROP-ASI will be applied to standardize the assessment of sociodemographic data and AUD severity across all sites.

#### Clinical outcome measures

##### Primary outcome: alcohol consumption

Alcohol consumption measures will be derived from the Timeline Followback (TLFB). The TLFB method involves using a calendar to identify alcohol consumption patterns in terms of number of drinks per day during the last 30 days [38, 39]. One drink is defined as 12 g of ethanol.

##### Secondary outcome: cravings, self-efficacy, impulsivity and depressive severity

The Visual Analogue Scale (VAS) comprises single-items used to measure the degree of alcohol cravings on scales ranging from 0 to 100, with 0 representing no cravings and 100 an extreme degree of cravings. The scale is presented visually on a ruler, and the individual will be requested to report the mean level and the peak level of cravings experienced during the last 30 days [40, 41].

The 14-item obsessive-compulsive drinking scale (OCDS) measures the degree of cravings experienced during the last 7 days. Items are rated on scales ranging from 0 to 4. The higher the score, the more pronounced the cravings. The scale has two subscales: obsessive cravings score and compulsive cravings score. A total score is calculated based on these subscales, and it is possible to calculate a resistance/impairment and interference subscale score [42].

The 40-item Alcohol Abstinence Self-Efficacy Scale (AASE) measures current level of temptation to drink alcohol and self-efficacy to abstain from drinking. The scale applies 20 situations representing typical drinking cues. Twenty items pertain to temptation levels, the other 20 items to self-efficacy. Items are rated on scales ranging from not at all (0) to extremely (4). The measure comprises the following sub-scales: (1) negative affect; (2) social interaction and positive states; (3) physical and other concerns; and (4) withdrawal and urges [43].

The 30-item Barratt impulsiveness scale (BIS, Patton, Stanford, & Barratt, 1995) assesses dimensions of impulsivity using three subscales: (1) attentional (attention and cognitive instability), (2) motor (motor and perseverance); and (3) non-planning (self-control and cognitive complexity). Items are rated on 4-point Likert scales ranging from 1 = very true for me to 4 = very false for me [44].

The Beck Depression Inventory-II (BDI-II; Beck et a., 1996) is a 21-item multiple-choice instrument that measures the severity of depression. Each item is rated on a 4-point scale ranging from 0 to 3 based on severity [45].

#### Experimental outcomes

##### AAT and diagnostic-AAT-VR

The conventional AAT will be applied as described in Conventional approach- avoidance training program section. The application of the VR-based AATP will be described in Approach- avoidance training program in virtual reality section. The TAU group will be randomized to either the PC or VR AAT bias assessments as described in Treatment as usual. The stimuli in the AAT and AATP stimuli consist in known brands or stimuli that are easily recognized (see Supplementary material for further description and pictures of the stimuli [33]).

##### Cue-induced cravings

Cravings will be assessed for all alcoholic and non-alcoholic beverages from the stimuli-relevant conventional and VR-based AATP. The pictures will be rated on the VAS scale ranging from 0 to 100 according to the immediate level of craving induced to examine their potential to elicit cue-induced cravings.^1^

##### Response inhibition

Response inhibition towards alcohol cues will be recorded using a modified version of the classical Go/No-Go Task [46, 47]. The modification involves the use of alcohol-related and neutral pictures to specifically test inhibition capacities towards alcohol-related cues. Pictures of alcoholic and non-alcoholic drinks from the conventional and VR-based AAT as well as new pictures will be included in the task. Patients will be instructed to respond as fast as possible, and without errors, by pressing a response button when they see a non-alcoholic drink (i.e. “Go” signals) but to withhold their response when an alcoholic drink is presented (i.e. “NoGo” signals) (see Supplementary material for further description of the parameters [33]).

### Data management

All data collected in the study will be treated as strictly confidential and the data collected by research assistants will be entered in a secure database. Before extraction or transferring data across sites, data will be anonymized (person sensitive data) and encrypted (group allocation) by an external data manager and transmitted through secure pathways. Researchers responsible for reporting the results will not have access to the data and will receive the analysis in their final form for reporting. All procedures are approved by the research ethics committee in each of the participating countries (see Ethics section).

### Statistical analysis

Descriptive statistics will be calculated to summarize socio-demographic factors, AUD diagnosis and psychiatric comorbidity as well as primary and secondary measures at baseline. Categorical variables will be described using frequencies and percentages. Normally distributed numeric variables will be described using the mean/standard deviation (SD), non-normally distributed numerical variables using the median/interquartile range (IQR).

The main analyses will be conducted with a repeated measures ANOVA, with group as the between-subjects factor and drinks per day the last 30 days at each assessment time-point as the within-subjects factor, to test the effectiveness of the intervention across the assessment points, which would be indicated by a significant Time X Study Group interaction. If there is an overall significant interaction effect between any one time-point and group, we will examine whether the change over time differs between the groups and the time-point using contrasts. Secondary analysis of continuous outcomes will be conducted with repeated measures ANOVA models, with group as the between-subjects factor and other alcohol consumption- (drinking days and drinks per drinking day), craving-, impulsivity- and depressive symptom outcomes as the within-subjects factor. In the case of unbalanced attrition in the randomization groups, mixed models will be applied instead of repeated measures ANOVA. Secondary analysis of dichotomous outcomes (e.g. relapse) will be conducted using mixed model logistic regressions. The analyses will be adjusted for the randomization stratification variable, site, as well as for the outcome values at baseline [48]. Since the study is a randomized controlled trial, other covariates are expected to be balanced across the randomization groups. Missing data will be handled using multiple imputation with changed equation (MICE) methods applying the non-parametric predicted mean matching (PMM) methods [49].

All analyses will be conducted as intention to treat as well as per protocol, and subgroup analyses will be conducted on patients who were successfully treated with conventional or VR-based AATP, defined as completing all six sessions. Further, moderation analyses of approach bias and using anti-craving medication on the treatment effect will be conducted for the primary and secondary outcomes.

When performing the descriptive and inferential analysis, the researchers will be blinded to the experimental and control groups, and an external statistician will conduct the analysis. The significance level in the models will be set at 5%, and two-sided analyses will be conducted. Effect sizes will be reported in accordance with the statistical modelling. All analyses will be conducted using Stata 16.

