### Treatment as usual at the inpatient alcohol clinics

In all three countries, treatment as usual (TAU) consists mainly of psychological treatment which in some cases is combined with pharmacological treatment in accordance with the NICE guidelines [31]. At treatment entry, the patient is offered detoxification (e.g. diazepam, lorazepam, oxazepam or clomethiazole), and other pharmacological treatment (e.g. acamprosate, naltrexone or disulfiram) is provided to support abstinence if needed. The psychological treatment consists mainly of CBT applied during hour-long individual or group sessions. In Germany, TAU lasts for approximately 1 month, whereas in Poland it lasts for approximately 2 months and Denmark it lasts for approximately 3 months. The inpatient treatment in Germany is shorter due to a shorter coverage of the health insurance. Although patients are encouraged to strive for abstinence, the treatment goal for some patients is moderate drinking, defined as not drinking more than five drinks per occasion. In all countries, the treatment strategy is planned together with the patient and typically incorporates psycho-education, functional analysis of drinking situations, development of coping strategies, problem-solving, and homework between sessions.

The psychological treatments are delivered by trained therapists encompassing nurses, social workers and psychologists. Supervision takes place frequently and psychiatrists and clinical psychologists monitor the treatment course regularly.

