#### Power analysis

The present study is the first to focus exclusively on stimuli-relevant AATP training in addition to TAU in clinical AUD patients, and only one prior study has examined the stimuli-relevant AATP training [26]. This prior study was conducted among subclinical AUD individuals and used a continuous drinking (drinks per day) measure as an evaluation of a stand-alone stimuli-relevant AATP over the web. A small effect at post-treatment (f = 0.17) and close to a medium effect at 3-month follow-up (f = 0.22) was identified [26]. Since our study is targeting a clinical sample with a higher degree of alcohol consumption, it may be easier to detect an effect than in a subclinical AUD sample, however, the AATP training in our study is provided as an add-on to TAU which could dilute the treatment effect compared to the prior study. To be conservative, we only aim to achieve a small additive effect at 3-months follow-up. Since pre- and post-treatment assessments of our intervention are conducted in an inpatient setting rather than over the web, attrition is mainly an issue at the 3-months follow-up assessment. Therefore, we collect only the clinical outcomes that can be measured in a variety of settings (e.g. at treatment, at home, over the phone or through a link on the web). An attrition rate of 30% at 3-month follow-up is assumed.

Based on this, a power analysis (PA) [50, 51] was conducted using G*Power for a repeated-measures ANOVA with α = 0.05; effect size (ES) of f = 0.17; power = 0.80; groups k = 3; time-points measurements = 3; correlations among repeated measures = 0.40; and nonsphericity correction E = 0.60, resulting in a sample size of *n* = 123 participants. To allow for adjustment of the stratification variable, site, an extra 20 patients are required for the final analysis (total *n* = 143). Finally, to account for an attrition rate of 30%, the required sample size is 204 (= 143/(1–0.3)) patients, corresponding to 68 patients in each group.

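### The primary three-visit Time x Group interaction is a weak test of an effect expected at 3 months: 27-36% power for a T3-only f = 0.17, against 49% for a baseline-adjusted T3 comparison

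*Protocol article*

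**What the plan says.** - **Model.** Statistical analysis: "The main analyses will be conducted with a repeated measures ANOVA, with group as the between-subjects factor". Drinks per day at each assessment is the within-subjects factor. A significant Time x Group interaction indicates effectiveness, and contrasts follow only then. Their error term is not named. "The significance level in the models will be set at 5%, and two-sided analyses will be conducted".
- **Baseline.** The same section adjusts the analyses for site and for the baseline value of the outcome. Mixed models replace the ANOVA only if attrition is unbalanced between groups. Non-normality is addressed for descriptive summaries, not for the primary model.
- **Outcome.** Primary outcome: alcohol consumption: "number of drinks per day during the last 30 days".
- **Timing.** Treatment as usual: "In Germany, TAU lasts for approximately 1 month", with about 2 months in Poland and 3 in Denmark. Experimental and control groups: training starts about 3 weeks before discharge. Power analysis: the pre- and post-treatment assessments take place in the inpatient setting.
- **Target.** Power analysis aims at a small additive effect at 3 months. The hypothesis in the Discussion is also placed there.
- **Sample size.** The inputs are "repeated-measures ANOVA with α = 0.05; effect size (ES) of f = 0.17; power = 0.80; groups k = 3". Three visits, a correlation of 0.40 between them and an epsilon of 0.60 complete the list. The result is 123, then 143 evaluable after 20 are added for site, then 204 randomized for 30% attrition.

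**The concern.** The question is asked at T3, but the test asks whether the groups' profiles differ anywhere over T1, T2 and T3. Randomized groups should not differ at T1. At T2 most of the recall window is spent as an inpatient, so there is little room for a difference in drinking. An effect that shows only at T3 is then diluted across the interaction's degrees of freedom and set against the between-patient spread of baseline drinking. Because contrasts wait for a significant interaction, a real T3 difference can go unreported. A second question is whether follow-up contrasts would have correct standard errors when the spread of drinks per day differs greatly between visits.

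**Working it through.** **1. Reproduce the plan's figure.** Within-between interaction with k = 3 groups, m = 3 visits, f = 0.17, correlation 0.40, epsilon 0.60:

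lambda = f² x N x m x epsilon / (1 - rho); df1 = (k-1)(m-1) x epsilon = 2.4; df2 = (N-k)(m-1) x epsilon.

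At N = 123: lambda = 0.0289 x 123 x 3 x 0.60 / 0.60 = 10.66, df2 = 144, power 81%. The smallest N for 80% is 121, or 123 in equal groups. The stated 123 reproduces, so f = 0.17 was entered as the size of the interaction.

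**2. Convert a T3-only effect.** If the group means deviate by d at T3 and by nothing at T1 and T2, the interaction terms are 2d/3 at T3 and -d/3 at each other visit. Their mean square is (4/9 + 1/9 + 1/9)/3 = 2/9 of d². So interaction f = T3 f x sqrt(2/9) = 0.471 x T3 f. A T3 f of 0.17 becomes 0.080, and 0.22 becomes 0.104. Conversely, an interaction f of 0.17 needs a T3-only f of 0.17/0.471 = 0.36.

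**3. Power at N = 143, normal data, correlation 0.40.**
- Interaction, T3 f = 0.17, epsilon 0.60: lambda = 0.00642 x 143 x 3 = 2.76, df 2.4 and 168, power 27%.
- Interaction, epsilon 1: lambda = 2.76/0.60 = 4.59, df 4 and 280, power 36%.
- T3 comparison of three groups adjusted for baseline: lambda = 0.0289 x 143/(1 - 0.40²) = 4.92, df 2 and 139, power 49%.
- T3 f = 0.22: 43% and 58% for the interaction, 72% for the adjusted T3 comparison.

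**4. Skewed data.** The article gives no mean, SD or share of zeros at any visit, so these are assumptions: baseline mean 12 drinks per day, 90% zeros at T2, 50% zeros at T3, 48 patients per group. Power for a 25-point difference in T3 abstinence (50% to 75%), from simulation, with ranges covering separate runs:

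| Baseline SD | Interaction, epsilon-corrected | T3 adjusted for baseline |
|---|---|---|
| 4 | 34-36% | 41-43% |
| 8 | 12-15% | 42-43% |
| 12 | 7-9% | 43% |

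**5. Level under the null, same assumptions.** The epsilon-corrected interaction rejects in 4.4-5.9%. If contrasts used one error term pooled over visits, T1-T3 would reject in about 7-10% when run without the gate. T2-T3 would reject in 0.4-1.4% at baseline SD 8, about 0% at SD 12 and 5.9% at SD 4. Contrasts with their own error term stay at 4.3-5.7%.

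**The case against.** - **Is the plan invalid?** A reader might infer from the skewed, zero-heavy outcome that the repeated measures ANOVA is invalid and reports too many false positives. The documents do not support this. The corrected interaction holds about 5%, and the power calculation already allows for nonsphericity (epsilon 0.60). A pooled error term is the classical default, not something the article specifies. Even with it, the plan's gate limits a given T1-T3 contrast to about 2-3% under the global null. What remains is that pooled standard errors would be wrong if they were used: too small for T1-T3, and too large for T2-T3 when baseline SD is large.
- **Is skewness the cause?** Only in part. Step 3 uses normal data and already shows the loss. It comes mainly from keeping baseline as a repeated level and spreading a T3 effect over three visits.
- **Near-zero T2 is inferred.** This stands. Some patients aim for moderate drinking, and no share of zeros is given. T1 is not purely pre-treatment either: baseline follows detoxification, and enrolment within 2 weeks of standard treatment is allowed.
- **Baseline as covariate.** If baseline is only a covariate, the repeated levels are T2 and T3, and Time x Group is the T2-T3 contrast with a correct error term. With a near-constant T2 its power is close to the T3 comparison (41% against 42-43% at baseline SD 8). With equal variances and correlation 0.40 it is not: lambda = 0.0289 x 143/(2 x 0.60) = 3.44, df 2 and 139, power 36%. So this reading helps, but the article does not settle on it: the Power analysis counts three time points.
- **Trajectories.** The abstract speaks of comparing trajectories over time, which an interaction does test. The hypothesis and the target effect are nevertheless stated at 3 months.

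**Conclusion.** The point holds as a loss of power for the stated question, not as an error in the level of the test. On the protocol's own inputs, a T3-only f = 0.17 has 27-36% power through the interaction and 49% through a baseline-adjusted T3 comparison; at f = 0.22 it is 43-58% against 72%. This rests on reading the target as a T3 effect with none at T2. If 0.17 is truly the size of the three-visit interaction, the stated power stands. The larger gaps under skewed data depend on assumed distributions and shrink to a few points at baseline SD 4. Separately, Statistical analysis (baseline as covariate) and Power analysis (three time points) give baseline two roles that must be reconciled. I rate this a cheap improvement.

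**What to change.** Rewrite one paragraph of the Statistical analysis section:
- Use baseline drinks per day only as a covariate, and say so in the Power analysis too.
- Make the primary test the T3 difference in mean drinks per day, adjusted for site and baseline. Take it either from a T3 model with robust standard errors or from a T2/T3 mixed model with unstructured covariance.
- Do not make the T3 comparison conditional on the Time x Group interaction. The interaction can stay as a secondary description of trajectories.
- Give any remaining contrasts their own error term.

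No new data are needed. In simulation the T3 comparison with robust standard errors rejected in 5.3% under the null. The costs are slightly wider intervals in some settings, and a primary test that no longer matches the G*Power calculation. The stated power must therefore be redone, and the change does not by itself give 80% at f = 0.17 with 143 evaluable patients.

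### Baseline drinking is both a repeated response and a covariate; with covariates entered as main effects, the stated baseline and site adjustment does not act on the Time x Group test

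*Protocol article*

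**What the plan says.** In the Statistical analysis section of the Protocol article, group is the between-patient factor and "drinks per day the last 30 days at each assessment time-point as the within-subjects factor". The intervention's effectiveness is what is tested, "which would be indicated by a significant Time X Study Group interaction". If the interaction is significant, "we will examine whether the change over time differs between the groups and the time-point using contrasts". The section then states: "The analyses will be adjusted for the randomization stratification variable, site, as well as for the outcome values at baseline". It names no product of either covariate with time. Mixed models replace the ANOVA if attrition differs between arms, and missing values are multiply imputed.

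The Measures section lists the time-points for the clinical outcomes as T1 (baseline), T2 (post-treatment) and T3 (3 months). The Power analysis section uses "effect size (ES) of f = 0.17; power = 0.80; groups k = 3; time-points measurements = 3", a correlation of 0.40 and a nonsphericity correction of 0.60, which gives 123 patients. It then adds: "To allow for adjustment of the stratification variable, site, an extra 20 patients are required for the final analysis". That makes 143, or 204 after allowing for 30% attrition.

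**The concern.** The baseline value stands on both sides of the model. In a repeated-measures ANOVA, Time x Group is tested within patients. Site and baseline are constant within a patient, so as main effects they can explain only differences between patients, which that test has already removed. Read literally, the plan promises an adjustment that its primary test does not receive.

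Precision at 3 months is at stake, since that is the time-point at which the plan seeks its effect and states its hypotheses, including VR against PC training. A T3-minus-T1 change leaves chance baseline differences in the estimate, and at a modest correlation it is noisy. The text is also loose enough for two analysts to fit different primary models from it.

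**Working it through.** **1. The plan's own figure.** Inputs from the Power analysis section: alpha 0.05, f = 0.17, power 0.80, k = 3 groups, m = 3 measurements, correlation rho = 0.40, correction eps = 0.60. For the within-between interaction:

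- noncentrality = f² x N x m x eps/(1 - rho)
- df1 = (k - 1)(m - 1) x eps = 2 x 2 x 0.60 = 2.4
- df2 = (N - k)(m - 1) x eps

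The smallest N is 121, which rounds up to 123 for three equal groups. At N = 123 the noncentrality is 0.0289 x 123 x 3 x 0.60/0.60 = 10.66, df2 = 120 x 2 x 0.60 = 144, and power is 0.81. The within-factor option gives 99 and the between-factor option 204. So 123 is the Time x Group test with baseline as one of three levels and no covariates.

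**2. Do the covariates act on that test?** Complete data were simulated with three groups, three sites and rho = 0.40, and the within-patient part of the ANOVA was fitted. The results for the Time x Group F were:

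| Patients | No covariates | Site + baseline as main effects | Site x time + baseline x time added |
|---|---|---|---|
| 143 | 2.429 (4, 280 df) | 2.429 (4, 280 df) | 3.695 (4, 274 df) |
| 144 | 4.89 (4, 282 df) | 4.89 (4, 282 df) | 7.15 (4, 276 df) |

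The equality of the first two columns is algebraic: a term constant within a patient lies in the span of the patient effects. It is exact for complete or imputed balanced data. In the 143-patient set, the T3-minus-T1 contrast adjusted for baseline and site equals the T3 ANCOVA exactly (SE 0.184), against SE 0.218 for the unadjusted change.

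A random-intercept mixed model with T1 still in the response behaved the same way. The interaction estimates were identical with and without the covariates, and the SEs were 0.2157 and 0.2151. Adding baseline as a covariate drove the random-intercept variance from 0.37 to zero, a sign that the specification is incoherent.

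**3. Precision of a pairwise T3 contrast.** Assume a common variance (set to 1) at T1 and T3 and correlation rho between them:

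- change from baseline: 2(1 - rho) = 2 x 0.60 = 1.20
- T3 alone: 1.00
- T3 with baseline as covariate: 1 - rho² = 1 - 0.16 = 0.84
- ratio of change to ANCOVA: 2(1 - rho)/(1 - rho²) = 2/(1 + rho) = 2/1.4 = 1.43

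The ratio is 2/1.2 = 1.67 at rho = 0.2 and 2/1.8 = 1.11 at rho = 0.8. Change is noisier than T3 alone only when rho is below 0.5. If the two SDs differ (s1 at T1, s3 at T3), the excess variance of change over ANCOVA is (s1 - rho x s3)², which is never negative. The direction therefore does not depend on equal variances, but the size does.

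With 143 completers (143/3 = 47.7 per arm), the difference detectable with 80% power at two-sided 5% is (1.960 + 0.842) x sqrt(variance) x sqrt(2/47.7). This is 0.63 SD for change and 0.53 SD for ANCOVA.

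**4. The 20 patients for site.** As a main effect, site has no role in the interaction test, so that test needs no allowance for it. The 20 patients raise the power of the unadjusted interaction from 0.81 at 123 to 0.87 at 143. After the attrition allowance they amount to 20/0.7, or about 29, enrolled patients.

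**The case against.** The strongest objection is that the drop-out depends on a model form the article does not spell out. In a conventional multivariate repeated-measures ANCOVA, covariates are applied to every within-patient contrast, so they do interact with time. The adjustments then act, as the last column of the table shows. The section also cites an outside source for the adjustment, and an analysis plan that is not shown may settle the form. This stands: the drop-out is conditional, and the absence of a site x time term from an article is not in itself an error. What remains is stated rather than omitted. The same baseline value is listed as response and as covariate, and the power calculation is for the unadjusted three-level test.

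A reader might go further and infer that the primary test is biased, invalid or underpowered. The documents do not support that. Under randomisation a Time x Group test with baseline as a level is valid, and the sample size was computed for that test. Nor may the 1.43 ratio be read as a loss in the primary test. It describes single pairwise contrasts at T3, whereas the primary test is an omnibus interaction on 4 df, for which no loss has been calculated.

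The variances are not fixed by the protocol either. Equal variances with a common correlation would give a nonsphericity value of 1, and the plan uses 0.60, so its own inputs do not fit that structure. Finally, usual treatment lasts about 1, 2 or 3 months by country, so site-specific trajectories are plausible, but the documents give no figure from which to size their effect.

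**Conclusion.** The concern holds in conditional form and should be fixed. Baseline is both a response level and a covariate. If the covariates enter as main effects, neither adjustment reaches the Time x Group test or the T3-minus-T1 contrast, and the 20 patients added for site have no role as an allowance in that test. The mixed-model fallback has the same problem if T1 stays in the response.

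The cost is precision at 3 months: 1.43 times the ANCOVA variance for a pairwise contrast, with a range of 1.67 to 1.11 over correlations of 0.2 to 0.8. This rests on equal variances at T1 and T3, and the 1.43 also on a T1-T3 correlation of 0.40. Validity and the power claimed for the unadjusted interaction are unaffected.

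**What to change.** State one model in which baseline has a single role. Either of these would do:

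- **T2 and T3 as the responses**, with group, time, group x time, baseline x time and site x time. The T3 group contrasts are read from this model. Time x Group would then ask only whether the group effect differs between T2 and T3, so the sentence naming it as the test of effectiveness must change too.
- **T1, T2 and T3 as responses in a constrained longitudinal model**, with a common baseline mean across groups and site x time, and without the baseline covariate. Time x Group can then remain the test of effectiveness, with the T3 contrasts taken from it.

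Use the same model for the continuous secondary outcomes and for the mixed-model fallback. Reword the power paragraph to name the test and covariates it refers to and what the extra 20 patients are for.

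The cost is rewording the analysis and the power basis. No new data or patients are needed. The change should be made before unblinding.
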